### Interventions

2.4.

After randomization into two groups, the enrolled patients will undergo routine preoperative preparation, including blood biochemical tests, and antibiotics will be administered once 30 min before surgery. All patients will undergo general anesthesia under tracheal intubation and receive T4 and T5 paravertebral nerve block. The SINTNP group will undergo left-side single-incision nonthoracoscopic-assisted Nuss surgery in accordance with our previous report (10). The TNP group will undergo thoracoscopic-assisted Nuss surgery with bilateral incisions, with the endoscopic observation hole on the right side. We need to emphasize that any child who requires the use of two bars during surgery will be withdrawn from the study cohort. After postoperative resuscitation, the patient will return to the ward and use a pain pump within 48 h after surgery.

One day after the surgery, chest radiograph bedside ward examination will be conducted. Starting from the second day after the surgery, a VAS pain score will be collected every morning. Those with a score of three or less will undergo the 100-meter walking experiment. Those who can successfully complete the 100-meter walking experiment independently and do not report any special discomfort will undergo chest radiograph examination. Those who had no obvious pneumothorax, pleural effusion, or steel plate displacement were discharged the next morning. If the child has a clear tendency toward plate allergy, such as extensive redness and swelling of the anterior chest wall skin or poor wound healing, such as incision suppuration, the patient will withdraw from the study. Their data will not be included in the analysis of pre-protocol set but will be truthfully reported and analyzed in the final research report of full analysis set.

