#### Coprimary outcomes

2.5.1.

Thoracic-related complications include pleural effusion, pneumothorax, and pneumonia diagnosed on chest radiograph.

Medical expenses during hospitalization are the total expenses recorded in the hospitalization electronic system, all of which are the original expenses before insurance reimbursement and are denominated in RMB.

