### Sample size and recruitment

2.6.

Medical expense during hospitalization is the primary outcome indicator of this study because it can objectively evaluate the financial burden of the patient's family. Based on our retrospective research data on surgeries over the past three years, the average cost of the TNP group was 30,250 RMB, while the average cost of the SINTNP group was 28,157 RMB. The standard deviation will be set as 2,000, and the superiority margin will be set as 1,500. The sample size will be calculated to require at least 141 children in each group.

The proportion of thoracic-related complications was approximately 9.6% in SINTNP and 13.6% in nonthoracoscopic-assisted Nuss surgery with double incision. The sample size calculation requires over 3,000 people per group according to the proportion of thoracic-related complications, and currently, we are unable to recruit so many patients. We will truthfully describe this recruitment-related limitation in the officially published article. Considering a 10% to 15% withdrawal and dropout rate, each group will ultimately include 160 children.

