### Masking

2.9.

Radiologists, nurses, and data analysts will be blinded to group information. The label of group was open for doctors and family members of children's guardians. The outcome will be assessed blindly by a statistician who is blinded to the group information. After data analysis, the results of the group information will be unblinded by the director of the trial. At this point, all participants in the study can receive detailed labels of grouping information.

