### Statistical methods

2.11.

Continuous data will be presented as the means with standard deviations (SDs) or medians with interquartile ranges (IQRs). The Kolmogorov–Smirnov test will be used to evaluate normality. Continuous data will be compared between the two groups by unpaired t test (normal distribution) or the Mann‒Whitney *U*-test (nonnormal distribution). A chi-square test will be used to compare categorical variables between two groups. Pre-protocol analysis (PP) will be performed with data of participants finishing the whole study and intention to treat analysis (ITT) will be used in full analysis set. Inter group analysis across centers were performed to evaluate the influence of bias and the reliability of the overall study.

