## Discussion

4.

Heart injury is the most dangerous complication of pectus excavatum, so all surgeons will do their best to avoid it (12). A practical and feasible approach is to observe through thoracoscopy (13). Through thoracoscopy, the surgeon can clearly observe the process of tunnel establishment and bar passing through the sternum. Aberrant vessels detected in the mediastinal pleura could be evaded under direct visualization during mediastinal dissection with thoracoscopy (14). Additionally, it is traditionally believed that the bar needs to be fixed bilaterally to avoid displacement, so thoracoscopy usually does not add additional incisions. Thoracoscopic assistance is necessary in adults, especially in patients with recurrence, history of previous thoracic procedure or double-bar insertion (7, 15).

However, for children who undergo their first surgery and only need to use one bar in preoperative evaluation, thoracoscopic assistance may be redundant. Children's sternum is relatively soft and malleable, and separation behind the sternum is usually safe. Especially considering the recent use of single-incision Nuss surgery, thoracoscopic assistance is difficult and may not be necessary (10). We are worried that the thoracoscope entering the pleural cavity will cause additional pulmonary complications. Excessive pain and prolonged hospital stay time may reduce the quality of life of the patient and parents after surgery, while also increasing the workload and burden of clinical doctors. We hope to reduce the surgical costs and postoperative hospital stay of the patient. In a relatively underdeveloped region such as western China, a considerable proportion of patients still struggle to bear the cost of surgery (16). Therefore, we must strive to reduce their burden.

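### Children found in theatre to need two bars are withdrawn from the cohort after randomisation, which on the plainer reading is incompatible with the planned intention-to-treat analysis and can bias the expense comparison in either direction

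*Protocol article*

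**What the plan says.** Section 2.4 (Interventions) of the protocol article sets the order of events: "After randomization into two groups, the enrolled patients will undergo routine preoperative preparation". Table 1 places randomisation on D0 and surgery on D2. The same section then says that "any child who requires the use of two bars during surgery will be withdrawn from the study cohort".

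Later in section 2.4 a second rule withdraws children with a clear tendency to plate allergy or with poor wound healing. Directly after it comes the retention sentence: "Their data will not be included in the analysis of pre-protocol set but will be truthfully reported and analyzed in the final research report", where the report meant is that of the full analysis set. No such sentence accompanies the two-bar rule.

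Section 2.11 (Statistical methods) says that "intention to treat analysis (ITT) will be used in full analysis set" and reserves the per-protocol analysis for participants who finish the study. It does not say who belongs to the full analysis set. Section 2.9 (Masking) states: "The label of group was open for doctors and family members of children's guardians".

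The Discussion describes thoracoscopic assistance as possibly redundant "for children who undergo their first surgery and only need to use one bar in preoperative evaluation". Section 2.3 (Eligibility criteria) contains no one-bar criterion.

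**The concern.** The need for a second bar comes to light during the operation, when the allocation is known. One arm operates with a thoracoscope and bilateral incisions, the other without a thoracoscope through a single left incision. The finding that triggers withdrawal can therefore depend on the arm, unlike an exclusion settled before randomisation.

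If the withdrawn children are left out of the full analysis set, the groups compared are no longer the groups that were randomised. Children who need a second bar may well be the longer and more expensive cases. A technique that led to more of them would have those cases taken out of its own results. This affects both co-primary outcomes (expense and thoracic complications) and both secondary outcomes (surgery duration and length of stay).

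Nothing in data collection forces the loss. Section 2.5.1 says: "Medical expenses during hospitalization are the total expenses recorded in the hospitalization electronic system". That record exists for every operated child, and the outcomes are collected in hospital.

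**Working it through.** **1. Reading the two rules side by side.** Both are in section 2.4.
- Allergy or wound rule: the child withdraws from the study, is left out of the per-protocol set, and is kept in the full analysis set.
- Two-bar rule: the child is withdrawn from the study cohort, and neither analysis set is mentioned.

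The retention sentence opens with a pronoun that refers to the children just named, the allergy and wound cases. Only a generous reading extends it back to the two-bar children.

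**2. Reproducing the plan's sample size.** Inputs from section 2.6: mean expense 30,250 RMB (TNP) and 28,157 RMB (SINTNP), SD 2,000, superiority margin 1,500.
- Expected saving: 30,250 − 28,157 = 2,093 RMB.
- Headroom over the margin: 2,093 − 1,500 = 593 RMB.
- n per arm = 2 × (1.645 + 0.842)² × 2,000² / 593² = 140.7, so 141, as stated.

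Alpha and power are not stated. One-sided 5% with 80% power reproduces 141; one-sided 2.5% or two-sided 5% with 80% power would give 179. The former is used below as an inference.

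**3. Bias from leaving two-bar children out.** Let p be the two-bar rate in an arm and c the mean extra cost of its two-bar children over its one-bar children. The arm's all-randomised mean is its one-bar mean plus p × c. So:

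saving in all randomised = saving in one-bar children + (p_TNP × c_TNP − p_SINTNP × c_SINTNP)

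If rates and extra costs are equal, the bracket is zero and the mean difference is not biased. If the product is larger in SINTNP, leaving these children out flatters SINTNP. If it is larger in TNP, it penalises SINTNP.

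The document gives neither p nor c. **Assumed range:** rates differ by 1 to 3 percentage points, and the extra cost is 5,000 to 15,000 RMB in both arms. The bias is then 0.01 × 5,000 = 50 RMB to 0.03 × 15,000 = 450 RMB.

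**4. Effect on the test at 141 per arm.** SE = 2,000 × √(2/141) = 238 RMB.
- Error when the true saving equals the margin and the bias b favours SINTNP: 1 − Φ(1.645 − b/238).
- Power when the same bias runs against SINTNP: Φ((593 − b)/238 − 1.645).

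| Bias b (RMB) | One-sided error at the margin | Power |
|---|---|---|
| 0 | 5% | 80% |
| 50 | about 8% | about 74% |
| 200 | about 21% | about 50% |
| 450 | about 60% | about 15% |

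**5. Cost of keeping these children.** With rate p and extra cost c, the arm's SD becomes √(2,000² + p(1 − p)c²). Holding the net difference at 593 RMB with 160 analysed per arm:

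| Two-bar rate | Extra cost (RMB) | SD (RMB) | Power |
|---|---|---|---|
| none | – | 2,000 | about 84% |
| 1% in each arm | 5,000 | about 2,060 | about 82% |
| 1% in each arm | 10,000 | about 2,230 | about 77% |
| 5% in each arm | 5,000 | about 2,280 | about 75% |
| 3% in one arm only | 15,000 | about 3,250 in that arm | about 63% |
| 3% in each arm | 15,000 | about 3,250 | about 50% |

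**The case against.** The strongest reply is that withdrawal in this document does not by itself mean removal from the full analysis set: the allergy and wound cases withdraw and are kept. Section 2.11 assigns intention to treat to that set, the text never says that two-bar data are discarded, and exact set membership is commonly left to the analysis plan. This stands in part. A reader might infer that the planned analysis is definitely not intention to treat, and the documents do not settle that. But the two-bar wording is the stronger of the two and has no retention clause, so the generous reading has to be supplied by the reader.

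A second reply is that the mechanism is inferred. No section names who decides on a second bar, says that the threshold differs by arm, or gives a rate or a cost. If preoperative evaluation already screens for one bar in practice, few cases would surface in theatre. This also stands: both the size and the direction of any bias are unknown.

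Two further inferences are tempting and unsupported.
- A reader might conclude that second bars would go unreported by arm. Nothing in the document says that withdrawals will not be counted.
- A reader might take the dropout allowance as the scale of the problem: "Considering a 10% to 15% withdrawal and dropout rate, each group will ultimately include 160 children". That is 32 to 48 of 320 children (0.10 × 320 and 0.15 × 320), but it covers all withdrawal and dropout. No share of it is attributed to two-bar cases.

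**Conclusion.** The point holds as a defect in a stated rule. Section 2.4 removes children after randomisation for a finding made during surgery, with the arm known, and on its plainer reading this is incompatible with section 2.11. On the generous reading, the primary analysis population is still left unclear. It needs correcting because it decides who is in the main comparison.

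The size is conditional. With equal two-bar rates and equal extra costs, mean expense is not biased. Under the assumed 50 to 450 RMB, the error at the margin is about 8% to 60%, or power is about 74% to 15%, depending on direction. These figures rest on the assumed rates and costs and on the inferred one-sided 5% and 80% power. They show that headroom of 593 RMB leaves little room for such a bias, not that one will occur.

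**What to change.** In sections 2.4 and 2.11, state that:
- every randomised child, including those found to need two bars, is analysed in the allocated arm in the full analysis set with the recorded expense, complications, surgery duration and stay;
- two-bar cases are left out of the per-protocol set only;
- the number of two-bar cases is reported by arm.

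Reconcile the Discussion's target group (one bar on preoperative evaluation) with section 2.3, which has no such criterion, so that any such restriction is settled before the envelope is opened.

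This changes who is analysed, not how any child is treated, and needs no new data. The price is variance. With 160 analysed per arm, power is about 77–82% if two-bar cases are rare (1% per arm, 5,000–10,000 RMB extra), about 75% at 5% and 5,000 RMB, and about 50–63% at 3% and 15,000 RMB. The scenario with the largest bias is thus also one in which the fix costs most power. The sponsor should look up the two-bar rate and its cost in its own retrospective data. Lost precision is not a reason to analyse a population selected after randomisation.

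Section 2.13 prohibits modification after publication, so the change needs a formal amendment or a definition of the full analysis set in the statistical analysis plan.

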### Monitoring

2.12.

A Data Monitoring Committee (DMC) will be established to ensure the wellbeing of study participants. The DMC will periodically review study progress and outcomes as well as reports of unexpected serious adverse events (SAEs). The DMC will, if appropriate, make recommendations to the Trial Steering Committee (TSC) regarding continuance of the study or modification of the study protocol.

When any SAEs occur, the researcher will immediately report it to the committee and be authorized by the committee to terminate the study. SAEs include (1) incision infection; (2) bar exposure; (3) bar displacement; (4) VAS score higher than 8 after using analgesic; and (5) obvious bar allergy. All adverse events will be truthfully recorded in the CRF form and reported in the final research results.

Independent investigators from the Ethics Committee of Children's Hospital of Chongqing Medical University will review the standardization of the study every two weeks and randomly observe the process of patient recruitment, doctor‒patient communication, surgical implementation, and outcome evaluation by researchers. Investigators will be independent to researchers and sponsors and will not sign their names in the final manuscript. We will thank them for their contributions to the research in the acknowledgment section.

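### A pain score above 8 is a reportable SAE, but no pain score is scheduled on the day of surgery or the day after

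*Protocol article*

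**What the plan says.** Section 2.12 (Monitoring) lists five kinds of SAE. The fourth is "4) VAS score higher than 8 after using analgesic". No time window is attached to it. When any SAE occurs, "the researcher will immediately report it to the committee and be authorized by the committee to terminate the study". The same section adds: "All adverse events will be truthfully recorded in the CRF form and reported in the final research results".

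Section 2.4 (Interventions) sets the pain assessment: "Starting from the second day after the surgery, a VAS pain score will be collected every morning". The score then opens the discharge pathway: "Those with a score of three or less will undergo the 100-meter walking experiment". On analgesia, section 2.4 says that after resuscitation "the patient will return to the ward and use a pain pump within 48 h after surgery". The one assessment it names for the first postoperative day is a bedside chest radiograph.

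Table 1 (section 2.5.3) matches this text. Surgery is marked at D2, the analgesic pump at D2 and D3, the chest radiograph at D3 and DN, and the VAS at D4, the daily column and DN.

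Section 2.9 (Masking) says "Radiologists, nurses, and data analysts will be blinded to group information", and of the treating side, "The label of group was open for doctors and family members of" the children's guardians. It does not say who takes the VAS.

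**The concern.** Most SAEs on the list can come to light without a dedicated measurement: an infected incision or an exposed bar can be seen, and a displaced bar can show on the scheduled radiographs. The pain SAE is different, because without a VAS there is no event to report. The fixed VAS schedule serves the walking test and discharge, and it starts after most of the period in which the protocol plans pump analgesia. SAE (4) was given no schedule of its own.

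An event that must be reported immediately, and that can lead to the study being stopped, should be looked for in the same way in both arms and all four hospitals. If a score on D2 or D3 is taken only when someone asks for it, capture may be incomplete. It may also be uneven between arms, because doctors and guardians know the allocation and the wounds differ: one left incision against bilateral incisions with an endoscope port on the right. The protocol gives no basis for saying which arm would be under-counted.

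**Working it through.** The plan gives no figure of its own to reproduce here. The check maps the schedule and then converts the gap to hours.

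**Schedule, from Table 1 and section 2.4**

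| Item | D2 (surgery) | D3 | D4 | Daily, to DN |
|---|---|---|---|---|
| Surgery | yes | | | |
| Analgesic pump | yes | yes | | |
| Chest radiograph | | yes | | DN only |
| VAS | | | yes | yes |

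Surgery is on D2, so the second day after surgery is D4, and text and table agree. The daily column stands after D4 and the text gives a starting day, so that column cannot be read as covering D2 or D3. Scheduled VAS on D2 and D3: 0 of 2 days.

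**Gap in hours**

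The protocol gives no clock times. Assumptions: surgery ends between 09:00 and 18:00 on D2, and the D4 morning score is taken between 07:00 and 10:00.

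Gap = 48 − (clock hour at which surgery ends) + (clock hour of the D4 score)

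- Shortest: 48 − 18 + 7 = 37 h
- Longest: 48 − 9 + 10 = 49 h

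**Share of the 48 h pump window already past at the first scheduled score**

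- Shortest gap: 37/48 = 77%, leaving 48 − 37 = 11 h
- Longest gap: 49 h exceeds 48 h, so 100%, leaving 0 h

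**With a D3 morning score added, on the same assumptions**

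- 37 − 24 = 13 h to 49 − 24 = 25 h after surgery

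A score on D2 after return to the ward would come earlier still.

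**The case against.** The strongest reply is that there is no error to correct. Text and table agree, and a journal article may leave ward pain observations to the full protocol. The morning VAS is a discharge gate, for which the second postoperative day is a sensible start. SAE (4) can be read as event-driven: a child in severe pain despite treatment is scored, and the general duties to report and record then apply. Unevenness between arms is conjecture, since nurses are listed as masked and both arms share the same schedule and pump. The hours above rest on assumed clock times and show no missed event. Pain is not an endpoint. Finally, section 2.13 bars changes to the protocol after publication.

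Much of this stands. There is no strict contradiction. An unscheduled score on D2 or D3 can trigger the SAE, the D4 score may still fall within the pump window, and later daily scores can also show it. Any imbalance has no known direction, and the protocol gives no rate of scores above 8.

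Two parts do not hold. First, the article is not silent on timing: it states a VAS start day in the text and again in the table, and that day skips most of the pump period. Second, the duties to report and record act on events already known and do not prompt anyone to take a score. The bar on changes is a real constraint, but section 3 states that the formal study had not started when the article was written.

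**Conclusion.** The concern holds as a modest point about safety capture. The protocol defines an SAE by a score and then schedules that score on neither of the two days on which the pump is marked. On the assumed clock times, the first scheduled score comes 37 to 49 h after surgery, with 0 to 11 h of the 48 h pump window left. That there is no scheduled score on D2 or D3 follows from the document alone; only the hours depend on the assumptions.

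The consequence is possible under-counting of SAE (4) in that period, perhaps unequal between arms. How many events would be missed cannot be estimated from the protocol. No primary or secondary endpoint, sample size or error rate is touched. The change is worth making because it costs little. Confidence is medium, because the protocol does not say who scores pain or what ward routine applies.

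**What to change.** - In section 2.4, Table 1 and the CRF, add VAS entries on D2 (after return to the ward) and on D3, taken by ward nurses at routine observations.
- In section 2.12, state that SAE (4) applies from return to the ward until discharge.
- Keep the D4 morning score as the gate to the walking test and discharge. Analgesic treatment does not change.

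The cost is two more marks in one row of Table 1, the matching CRF fields and a few bedside scores per child. The number of pain SAEs reported to the committee may rise. Wounds or dressings may still show nurses the arm, so a fixed schedule makes scoring more uniform but does not guarantee masked scoring. Given section 2.13, the change should be made and documented before enrolment. If the added scores are not wanted, the least that should be done is to state that SAE (4) is assessed only from D4, so that its count is read accordingly.

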**Methods:**

This study is a prospective, superiority, multicenter, non-masked, randomized controlled trial that investigates the outcome and hospitalization medical expense of SINTNP compared to TNP for PE. A total of 320 eligible patients according to sample size calculation by retrospective data will be randomly assigned to the SINTNP group or the TNP group at a 1:1 ratio using stratified blocked randomization and the zone length was set as four. Patients aged between 3 and 18 years old for the first surgery and without combination of complex anomalies such as Marfan syndrome and congenital heart disease will be considered for the study. The co-primary endpoint is thoracic related complications and medical expense during hospitalization. Thoracic related complications were defined as pneumothorax, pleural effusion, pneumonia and incision infection. The secondary endpoints include surgery duration and length of hospital stay.

The registration number for this study protocol is ChiCTR230073081 (Chinese Clinical Trial Registry, A Primary Registry of International Clinical Trial Registry Platform, World Health Organization).

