### Outcomes and participant timeline

2.5.

The outcome indicators will be extracted from the CRF table after the patient is discharged and then uploaded to the online web-based database. Confirmation of outcome data will be undertaken with an additional sign-off by the site's principal investigator for each participant.

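### The per-protocol set is selected on outcome: children with incision suppuration or plate allergy are removed from it, although these are results of surgery and not protocol deviations

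*Protocol article*

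**What the plan says.** Section 2.4 (Interventions) describes children who, after surgery, show a clear tendency toward plate allergy or "poor wound healing, such as incision suppuration, the patient will withdraw from the study". On the analysis sets it continues: "Their data will not be included in the analysis of pre-protocol set but will be truthfully reported and analyzed in the final research report of" the full analysis set. ('Pre-protocol' is evidently per-protocol.)

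Other parts of the article treat the same events as outcomes:

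- Section 2.12 (Monitoring): "SAEs include (1) incision infection; (2) bar exposure; (3) bar displacement", and further on in the same list, "5) obvious bar allergy".
- Abstract, Methods: "Thoracic related complications were defined as pneumothorax, pleural effusion, pneumonia and incision infection".
- Section 2.5.1 (Coprimary outcomes): "Thoracic-related complications include pleural effusion, pneumothorax, and pneumonia diagnosed on chest radiograph". Incision infection is absent here and from Table 2.

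Section 2.11 plans a per-protocol analysis of participants who finish the whole study and an ITT analysis in the full analysis set. It does not say which is primary. Section 2.5 adds: "The outcome indicators will be extracted from the CRF table after the patient is discharged".

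**The concern.** A per-protocol set is meant to exclude children whose treatment departed from the plan. A child with a suppurating wound or a reaction to the bar has had the allocated operation and then a bad result. Removing the child for that result selects the analysis set on an outcome, and randomisation no longer protects the comparison.

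The arms also differ in what could produce a wound event. Section 2.4 gives SINTNP one left-side incision, and TNP bilateral incisions with an observation hole on the right. Unequal removal is therefore possible, although the document gives no rates.

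At stake are the per-protocol results for complications, expense and length of stay. They carry weight because no set is named primary. In addition, the abstract calls the trial a superiority trial while section 2.2 announces noninferiority tests, so a reader cannot tell which analysis will carry the conclusion.

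**Working it through.** **1. Role of each event in the document.**

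| Event | Removed from per-protocol set (2.4) | SAE (2.12) | Co-primary, abstract | Co-primary, 2.5.1 and Table 2 |
|---|---|---|---|---|
| Incision suppuration/infection | yes | yes | yes | no |
| Plate (bar) allergy | yes | yes | no | no |

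If the rule is followed, recognised suppuration and clear plate allergy are zero in the per-protocol set in both arms, whatever the true rates. This needs no assumption.

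**2. The plan's own figure for expense (section 2.6).** Means are 30,250 (TNP) and 28,157 RMB (SINTNP), SD 2,000, margin 1,500.

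- Difference: 30,250 - 28,157 = 2,093. Headroom over the margin: 2,093 - 1,500 = 593.
- n per arm = 2 x (1.645 + 0.842)^2 x 2,000^2 / 593^2 = 140.7, rounded up to 141.

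This matches the stated 141. One-sided 5% and 80% power are inferred, since the article states neither.

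**3. How removal shifts the expense difference.** Let q be the fraction removed in an arm and e their mean excess cost over the children who remain. In each arm, full-set mean = per-protocol mean + q x e. Hence

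per-protocol difference - full-set difference (TNP minus SINTNP) = -(q_TNP x e_TNP - q_SINTNP x e_SINTNP).

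The document gives neither q nor e. The values below are assumptions, with the same e in both arms:

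| Removed, TNP / SINTNP | e = 2,000 | e = 5,000 | e = 10,000 |
|---|---|---|---|
| equal | 0 | 0 | 0 |
| 4% / 2% | -40 | -100 | -200 |
| 2% / 4% | +40 | +100 | +200 |

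As a share of the 593 headroom, 40, 100 and 200 RMB are 7%, 17% and 34%.

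**4. Limit on the assumptions.** If 2,000 is the SD of all children in an arm, the affected children cannot account for more than its variance: q(1 - q)e^2 must stay below 2,000^2 = 4.00 million. At q = 4% and e = 10,000 it is 0.04 x 0.96 x 10,000^2 = 3.84 million, which just fits. At e = 15,000 it is 8.64 million, which is impossible. The table therefore stops at 10,000.

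**5. Data after withdrawal.** Table 1 shows no visit after discharge, so the rule operates during the stay, while expense and length of stay are still accruing. Section 2.4 promises analysis in the full set, but no section says that collection continues after withdrawal.

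**The case against.** The strongest reply is that nothing is lost to the trial. Section 2.4 keeps these children in the full analysis set, section 2.11 applies ITT there, and section 2.12 promises that all adverse events will be recorded and reported. Both analyses will be shown, so a gap between them would be visible. This stands, and it confines the fault to the per-protocol set.

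Four stronger readings that a reader might infer are not supported:

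- *That co-primary events are omitted, without qualification.* This is true of suppuration only under the abstract's definition, and of allergy under neither.
- *That the set loses its most expensive children, or that the bias disfavours SINTNP.* Higher cost is plausible, but the document gives no cost or frequency. The shift can be zero or of either sign.
- *That a loss of power can be stated.* Holding the SD at 2,000 with and without the removed children is inconsistent. If 2,000 is the full-set SD, removal also shrinks the per-protocol SD. With 4% and 2% removed, 141 per arm and one-sided 5%, per-protocol power is then about 74% at 5,000 RMB excess and 93% at 10,000, against 80% planned. If 2,000 is instead the per-protocol SD, full-set power is already only about 74% and 60% at those costs. No single power figure follows.
- *That the full-set data will be truncated.* Expense comes from the hospital's electronic system and outcomes are extracted after discharge, so collection may well continue. The text merely leaves it unstated.

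**Conclusion.** The point holds in a limited form. The per-protocol set is conditioned on post-randomisation results of surgery. By construction it omits events that section 2.12 lists as SAEs and, under the abstract's definition only, co-primary infections.

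Any effect on expense and length of stay is of unknown size and sign. On the assumed inputs above the expense shift runs from 0 to 200 RMB in either direction, up to about a third of the 593 RMB headroom. It vanishes if rates and excess costs are equal between arms. The ITT comparison is protected provided that data are collected to discharge.

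The fault matters chiefly because neither set is named primary. It does not depend on the assumed figures: a set selected on complications is not a sound comparison whichever way the bias runs.

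**What to change.** In sections 2.4 and 2.11:

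- Name the full analysis set (ITT) as primary for the superiority comparison.
- Define per-protocol exclusions by protocol deviations only, never by complications.
- State that children with plate allergy or poor wound healing have expense, length of stay and complication data collected to discharge, are analysed in both sets, and have these events reported by arm.

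Reconcile the abstract with section 2.5.1 and Table 2 on whether incision infection belongs to the co-primary endpoint.

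This concerns study data and analysis sets only and leaves clinical management unchanged. The cost is wording, with no added visits or tests. Expense in the per-protocol set will be somewhat more variable. The Results section says that the study has not started, while section 2.13 bars modification after publication, so the change needs a documented correction before enrolment.
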